#### Intervention group

Adolescents, families, and school staff in the intervention arm have access to the IMPROVA platform, which includes both the intervention and information platforms, once baseline assessments are completed. In each participating country, a designated support person was available to provide technical assistance to users throughout the trial via email.

None of the intervention components of the IMPROVA programme was mandatory or required to be completed. Therefore, all users were free to choose which parts of the intervention programme they wished to explore or engage with. This flexible approach was designed to respect the diverse needs and contexts of users, and to promote autonomy, allowing each participant—whether adolescent, family member, or school staff—to engage with the content most relevant and useful to their specific circumstances and interests.

### Intervention implementation strategies

During the invitations for school enrolment, the local IMPROVA teams presented the project and its intervention content to school directors and teachers with administrative responsibilities (eg, head of education, coordinator). In Germany, at some schools, a social worker responsible for implementing health programmes at the school level carried out these meetings, and was the IMPROVA contact point. This difference between countries is due to the fact that IMPROVA was conceptualised to be adaptable to local characteristics. In Germany, the professionals responsible for secondary education in the region indicated that the best approach to implementing IMPROVA was through this professional.

After these presentations to the school directory board, teachers, adolescents, and families were introduced to the project during recruitment. In intervention schools, available intervention resources were highlighted. Presentation strategies were adapted to the country and school characteristics since it was imperative to adapt to local circumstances. For example, in Spain and France, the research team personally presented the project to students and school staff and conducted webinars with families. Alternative strategies included sending flyers and emails to participants.

During the school year, the local research teams had close contact with a designated school representative, who acted as the main contact point with the project. In some schools, the contact occurred via WhatsApp, while other schools preferred emails or phone calls. These interactions served to organise the distribution of communication material with teachers, students, and families of the IMPROVA intervention programme. Diverse strategies were implemented to increase the visibility of the programme, such as posting information about the IMPROVA intervention on the school website, distributing flyers via the school channels to each stakeholder, or directly sending emails to participants. Once a month, a blog post about topics of interest to adolescents (eg, ‘procrastination’ and ‘FOMO—Why it’s okay to miss out’) was uploaded to the information platform, which also promoted usage of the intervention platform. Throughout the school year, schools also received posters to display on classroom notification boards. All these strategies aimed to raise attention to the intervention programme and the number of resources available for each user type. In summary, each user type received at least one communication material from IMPROVA every month, either directly via email or indirectly (eg, posting on the school webpage, posters), aiming to disseminate the project.

### Outcomes and assessments

Overall mental health is the primary effectiveness outcome of the IMPROVA intervention programme. Secondary outcomes include HRQoL, depression, anxiety, social isolation, and self-esteem.

The assessments administered in IMPROVA include scales in various domains and were conducted at baseline (between November 2024 and March 2025), mid-term (during the intervention, March–May 2025), postintervention (immediately after the intervention, May–August 2025; primary endpoint) and 6 months postintervention (January-February 2026, secondary endpoint). Schools dedicated a school class for baseline and postintervention assessments, so teachers and/or IMPROVA staff could support students during assessments.

A description of the assessments conducted in the IMPROVA project is provided in the following sections.

#### Overall mental health

Overall mental health was assessed by the self-completion form of the Strengths and Difficulties Questionnaire (SDQ),^41^ a validated tool among adolescents aged 11–17. Adolescents rated their level of agreement with 25 items on a 3-point Likert scale ranging from 0 (‘not true’) to 2 (‘certainly true’). The 25 items represent five subscales, with scores ranging from 0 to 10: emotional symptoms, conduct problems, hyperactivity/inattention, peer problems, and prosocial behaviour.

The SDQ total score ranges from 0 to 40 points (sum of four subscales: Emotional Symptoms, Conduct Problems, Hyperactivity/Inattention, and Peer Relationship Problems). A higher score indicates poorer overall mental health. The Prosocial Behaviour Subscale score ranges from 0 to 10, and is interpreted separately. The SDQ score can also be categorised to facilitate interpretation. Initially, scores could be interpreted using a three-band categorisation: normal (0–15 points), borderline (16–19 points), and abnormal (20–40). Recently, a newer four-band categorisation has been used: close to average (0–14 points), slightly raised (15–17 points), high (18–19), and very high (20–40). Similar categorisation can also be conducted for each subscale of the SDQ.^42 43^ In addition, the SDQ also provides scores about internalising and externalising symptoms, each ranging from 0 to 20 points. The internalising score is the sum of the emotional and peer difficulties scales, whereas the externalising score is the sum of the conduct and hyperactivity scales. Finally, the SDQ contains an impact supplement, in which items on overall distress and impairment can be summed to generate an impact score that ranges from 0 to 10.

#### General HRQoL

The quality of life construct is assessed by three questionnaires: KIDSCREEN-10,^44^ the Cantril Ladder Scale^45^ and the Goal-Based Outcome Measure (GBO),^46^ since each assesses different domains of quality of life.

KIDSCREEN-10^47^ has 10 items and measures general HRQoL for adolescents. Each item on the KIDSCREEN-10 is rated on a 5-point Likert scale, reflecting the frequency or intensity of the feelings or behaviours described. The scores for the 10 items are summed to produce a total score between 10 and 50 points, where the higher the score, the higher the HRQoL. The total score can then be transformed into a T-score or percentile rank, based on normative data, to facilitate interpretation. In addition, KIDSCREEN-10 includes a general health question to provide an overview of the adolescent’s overall well-being.

The Cantril Ladder Scale^45^ consists of a visual representation of a ladder with steps numbered from 0 at the bottom to 10 at the top. Adolescents are asked to imagine that the ladder represents their life in two scenarios: (1) the present life evaluation and (2) future life expectations. The top of the ladder (step 10) represents the ‘best possible life’ they could imagine. The bottom of the ladder (step 0) represents the ‘worst possible life’ they could imagine.

The GBO^46^ is a method used to assess treatment progress and outcomes based on specific goals set by the adolescent. It is designed to capture changes in individuals’ functioning and well-being that are meaningful and relevant to them, rather than relying solely on standardised symptom measures. Adolescents are asked to select three goals they would like to achieve by the end of the current school year, and on a scale from 0 to 10, they choose the number that best describes how close they are to reaching their goal at that moment (0 means no progress has been made towards a goal, while a score of 10 means a goal has been reached fully).

#### Depression

The Patient Health Questionnaire-8 (PHQ-8)^48^ consists of eight items that correspond to the diagnostic criteria for major depressive disorder in the DSM-IV and DSM-5. Each item addresses a specific symptom of depression and is rated based on the frequency of the symptom over the past 2 weeks. Each of the items is rated on a 4-point scale. The total score ranges from 0 to 24. The total score is used to determine the severity of depression: 0–4: minimal or none, 5–9: mild, 10–14: moderate, 15–19: moderately severe, 20–24: severe. Adolescents with a score of 10 or higher will be considered as having a depressive disorder.^48^

#### Anxiety

The Generalised Anxiety Disorder-7 (GAD-7)^49^ consists of seven items that correspond to the diagnostic criteria for generalised anxiety disorder. Each item asks about the frequency of anxiety-related symptoms over the past 2 weeks. Each of the items is rated on a 4-point scale. The total score ranges from 0 to 21. The total score is used to determine the severity of anxiety: 0–4: minimal anxiety, 5–9: mild anxiety, 10–14: moderate anxiety, 15–21: severe anxiety. One question in the GAD-7 assesses the impact of anxiety on daily life.

#### Social isolation

The Social Isolation Questionnaire^50^ is composed of 17 items that can be categorised into three domains: feelings of loneliness, friendships, and family support. The score can assume values from 0 to 117, with lower scores indicating lower levels of social isolation.

#### Self-esteem

The Single-Item Self-Esteem Scale^51^ is a brief self-report measure designed to assess adolescents’ overall self-esteem with a single question. Adolescents rate their overall self-esteem on a scale ranging from one to seven, with higher numbers indicating higher self-esteem.

#### Adolescents’ mindsets towards change

For this domain, the 8-Item Implicit Theories of Intelligence Scale^52^ was administered. This scale includes eight items, four that reflect a fixed mindset and four that reflect a growth mindset. Each item is rated on a 6-point Likert scale, ranging from 1=strongly disagree to 6=strongly agree. Two separate scores (fixed and growth) and a total composite score will be obtained that can range from 8 to 48 points. A higher score represents a stronger fixed mindset, while a lower score represents a stronger growth mindset.

#### School environment

The School environment construct is assessed by two questionnaires: the Teachers and Classmate Support Scale^53^ and the 15-item School Engagement Scale.^54^

The Teachers and Classmate Support Scale^53^ is a measure designed to assess the perceived support that students receive from their teachers and classmates. It consists of two subscales: Teacher Support and Classmate Support. All items have a 5-point Likert scale. The ‘neutral’ category was not used in the IMPROVA survey. For each subscale, the scores for the individual items (1–5) are summed to obtain a total score (3–15). Higher scores indicate higher perceived support from teachers or classmates.

The 15-item School Engagement Scale^54^ is a self-report measure used to assess various dimensions of student engagement in the school environment. Developed to capture students’ psychological investment in learning and academic activities, the questionnaire evaluates multiple facets of engagement that contribute to positive educational outcomes. Scores are calculated by summing the responses across all items or within specific subscales, namely behavioural, emotional and cognitive. Higher scores indicate greater levels of engagement in the respective dimension.

#### Bullying

The revised Bully/Victim Questionnaire^55^ is a 4-item questionnaire to assess the extent to which adolescents engaged or were victims of bullying/cyberbullying. The items can be answered (and scored) on a 5-point Likert scale.

Table 4 describes the timepoint of each questionnaire and the respective domain of the IMPROVA assessment battery with adolescents.

**Table 4 T4:** Timeline, questionnaires and respective domains that composed the main assessments with adolescents

Domain	Questionnaire	Time points			
		Baseline	Mid-term	Postintervention	Follow-up
Overall mental health	SDQ^41^	x	x	x	x
General health-related quality of life	KIDSCREEN^44^	x	x	x	x
	Cantril Ladder Scale^45^	x	x	x	x
	Goal-Based Outcome Measure^46^	x	x	x	x
Depression	PHQ-8^48^	x	x	x	x
Anxiety	GAD-7^49^	x	x	x	x
Social isolation	Social Isolation Questionnaire^50^	x	x	x	x
Self-esteem	Single-Item Self-Esteem Scale (SISE)^51^	x	x	x	x
Mindset towards change	8-Item Implicit Theories of Inteligence Scale^52^	x		x	x
School environment	Teachers and Classmate Support Scale^53^	x		x	x
	15-item School Engagement Scale^54^	x		x	x
Bullying and cyberbullying	Revised Bully/Victim Questionnaire^55^	x		x	x

GAD-7, Generalised Anxiety Disorder-7; PHQ-8, Patient Health Questionnaire-8; SDQ, Strengths and Difficulties Questionnaire.

### Demographic data and other variables

Adolescents were asked about their sex, age and date of birth, school type (eg, public, publicly financed, private), grade (school class), country of birth, who they live with (mother (only), father (only), both parents, mother/father and a partner), parental marital status, number of siblings, languages spoken at home, the area where they live (rural or urban), and the Health Behaviour in School-aged Children (HBSC) family affluence scale.^56^

#### Substance use

At baseline and postintervention, adolescents aged 15 years or above were asked about their smoking and drinking habits by the following questions: smoking in the last 30 days (number of days), average number per day of cigars/cigarettes/electronic cigarettes and similar in the last 30 days (number of units/day), drinking alcohol in the last 30 days (number of days), and drinking alcohol at least five standard doses of alcohol in the last 30 days (number of days).

#### Chronic illnesses history

Adolescents were asked if they had been diagnosed with any of the following chronic illnesses by their physician: depression, anxiety, dyslexia/attention deficit hyperactivity disorder (ADHD)/learning problems, diabetes, respiratory problems (eg, asthma or others), migraine, no, other. When the ‘other’ option was chosen, adolescents could specify the chronic illness in a free-text field.

### Ecological momentary assessment

Ecological momentary assessment (EMA) and sensor data were embedded in the app version of the eSano component of the IMPROVA platform. In January 2025, EMA asked adolescents using the app about their sleep duration and quality, current emotions, and news exposure. In addition, on submission of each EMA questionnaire, sensor data on distance travelled and step count were recorded (see the following paragraph). When students logged into the app for the first time, they were asked for permission to send notifications for the EMA questionnaires and to use the specified sensors (ie, GPS and pedometer). For each permission, an explanation was displayed as to why this permission was needed and how the data would be used. These permissions were generally optional but required for the EMA and sensing features of the app to work properly. Students were free to decide whether to reject individual or all permissions without this having any negative consequences for the app’s remaining features or the main study. If the permissions were granted, during a 2-week period, the app notified students to complete EMA questionnaires at different time points and collect mobile sensor data. In IMPROVA, a notification was sent each morning, afternoon and evening. In the morning, a slightly different questionnaire with additional questions (eg, on sleep quality) was used.

### Data from sensor measurements

Sensor data on distance travelled (GPS) and step count (pedometer) were retrieved once at each questionnaire submission and transmitted together with the EMA answers. These sensor data can be used in analyses as a proxy for physical activity and, to a certain extent, as a proxy for adherence. No continuous or background sensor data collection was performed. Instead, discrete point-in-time measurements (step count and GPS position) were transmitted exclusively at the moment of questionnaire submission. Consequently, temporal trends in physical activity or mobility can only be inferred retrospectively by computing differences across multiple submitted measurements, provided that sufficient data points are available. The GPS geolocation data collected via the eSano app is anonymised (ie, rotated around the globe) and transmitted to the eSano platform exclusively in anonymised form. Anonymised locations within an app installation are all rotated by the same, initially randomly generated amount so that the distance between them is maintained. This means that the geolocation data collected can be used to calculate the distance travelled, but does not allow any conclusions to be drawn about specific places visited, in order to protect the privacy of users. For the pedometer data, the total number of steps since the permissions were granted is continuously recorded via the mobile operating systems’ application programming interfaces and at EMA questionnaire submission, the step count is retrieved and transmitted to the eSano platform. No additional processing is performed on the sensor data, and it is stored as-is alongside the EMA answers for later data analyses. Students are able to review their submitted EMA answers in the app, but the mobile sensor data are not displayed to the students to avoid unintentional focus on these data.

### Technical data on intervention uptake (students and teachers)

Another outcome of the study is the uptake of the intervention. For the intervention platform, this includes basic usage data on how often and how participants have used the platform (eg, number of modules completed, which modules were completed). For the information website, this usage data comprises the number and sequence of user visits and the point of access (ie, the region). This information is essential to evaluate the interactions between usage and effectiveness and to assess the effectiveness of the various modules.

We also included a battery of assessments with parents, school staff, and at the school level that might provide meaningful information about the trial and could support the evaluation of the trial, such as potential mediators or moderators of effect.

### Assessments exclusive with parents

Parents were also asked to answer a number of questions: degree of kinship, family income, age (date of birth), number of children, educational level of the parents, cost data (data regarding out-of-pocket expenses related to mental health and well-being of adolescents), and their relationship with their offspring assessed by the Child-Parent Relationship Scale^57^ (CPRS-SF), which includes a subset of items rated on a Likert scale. The CPRS-SF yields scores across two key dimensions: closeness and conflict. Higher scores on the conflict subscale suggest greater relational difficulties, while higher scores on the closeness subscale indicate a more positive parent–child relationship.

The abovementioned assessments with parents occurred at baseline, except for the CPRS-SF, that will also be administered at the postintervention period. The cost data will be assessed at postintervention.

### Assessments exclusively aimed at teachers and other school staff

School staff were asked sociodemographic questions such as sex, age, years of professional experience in their current position (in years and months), level of education (highest degree), school type (public, private, etc), school size (number of students), current position (eg, headmaster, teacher, psychologist, etc), and current discipline being taught (only for teachers).

In addition, school staff also answered questions about their health (burnout, self-efficacy and stress) and their perception of the school environment (school climate). Burnout was assessed using the Maslach Burnout Inventory–Educators Survey,^58^ which measures emotional exhaustion, depersonalisation, and personal accomplishment. Self-efficacy was measured with the Teacher Sense of Efficacy Scale,^59^ evaluating teachers’ beliefs in their ability to manage classrooms, engage students, and implement instructional strategies. Perceived stress was captured using the Perceived Stress Scale,^60^ which assesses the degree to which situations in one’s life are appraised as stressful. Finally, school climate was assessed with the CLIMATEB^61^ questionnaire, which evaluates teachers’ perceptions of the school’s social and organisational environment.

Implementation determinants will be examined. These are factors or conditions that influence whether and how well an intervention or programme is implemented in a specific setting. These determinants can act as barriers or facilitators to successful implementation. Key determinants are the programme’s perceived acceptability, appropriateness, and feasibility. School staff answered the Acceptability of Intervention Measure (AIM), the Intervention Appropriateness Measure (IAM), and the Feasibility of Intervention Measure (FIM) questionnaires^62^, and questions about barriers and facilitators^63^ for implementing the IMPROVA programme. Determinants were also assessed in terms of organisational readiness for change, using a 12-item questionnaire adapted for the school setting^64^ and measured among school directors at baseline. The questionnaire assesses aspects of readiness such as willingness, commitment and, preparedness to implement IMPROVA among staff members.

The abovementioned assessments with school staff occurred at baseline, except for burnout, self-efficacy, stress, school climate, appropriateness, acceptability and feasibility, and barriers and facilitators for implementing the IMPROVA programme, which also took place during the postintervention period.

### School-wide assessments

IMPROVA also includes assessments at the school level, which will complement individual data collection, to collect information about the possible implementation of concurrent mental health/well-being programmes, cases of bullying in the last 5 years, student absenteeism, school failure, students’ grades, among other parameters. The exact list of school-wide parameters to be recorded is still being defined.

### Cost data

Parents and school directors were asked about expenses related to the mental health and well-being of adolescents (eg, costs of programmes focused on promoting mental health and well-being, costs of training, workshops or materials used in school settings, and other related family- or school-level expenses). In addition to primary data collection, cost information will be supplemented with reports from specific countries and European cost reports to ensure a comprehensive basis for economic evaluation.

### Qualitative interviews

Interviews (1×1) and focus groups (up to 10 participants) will be conducted with volunteers from all stakeholder groups (adolescents, school staff, and families after the postintervention questionnaire). These interviews/focus groups will primarily focus on inquiring with users in terms of costs, impact, usability, acceptability, appropriateness, feasibility, costs, barriers and facilitators for implementation. These interviews/focus groups will be conducted in one session and will last a maximum of 60 min with a sub-group (at least 10–15 per user type and country) of participants. The procedures will be similar regardless of the type of user or the country where the interview/focus group is taking place.

### Statistical analyses

Descriptive analyses will be performed to summarise the sociodemographic variables and scales. Frequencies and percentages will be used for categorical variables, and means, SD, medians and IQRs, minimum and maximum for continuous variables. To evaluate baseline differences between the intervention and control groups the χ^2^ test or t-test will be applied.

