### Blinding, randomisation and allocation concealment

A statistician external to the IMPROVA project conducted the randomisation of schools into the intervention and control groups using a computer-based random number generator. The randomisation occurred before baseline assessments since we needed to be able to tailor the explanation and information of the project to participants according to their group allocation. For example, participants in the intervention group received a more detailed explanation on how to navigate the IMPROVA platform.

As planned, the statistician conducted a block randomisation at the country level in groups of four to eight schools, depending on the number of schools recruited at each trial site (country). In France, the second round of block randomisation needed to be adapted. In France, there are two types of secondary schools with distinct age groups of adolescents (collège: 11–14 years old; lycée: 15–18 years old); therefore, in the second round of randomisation in France, the randomisation was stratified depending on the type of secondary school to ensure an equal representation of younger and older adolescents in each group.

After the randomisation, the research team and participants were not blinded regarding school allocation.

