### Effectiveness analysis

The effectiveness of the IMPROVA programme will be evaluated based on improvements in overall mental health. Specifically, the primary analysis of effectiveness will be reflected in a reduction in the total SDQ score. In addition, effectiveness will be assessed through improvements in the secondary outcomes, as specified in a preceding section.

A linear mixed-effects model will be used to assess the effectiveness of the intervention on continuous outcomes (SDQ total score) measured across three assessment points, and generalised estimating equations will be used for categorical outcomes. Adolescents will be nested within schools, and schools will be nested within the four countries. A complementary analysis will include all four time points to evaluate the potential intervention effects at follow-up.

The model will include fixed effects for time, group (intervention vs control), and their interaction (group×time), which captures the differential change over time attributable to the intervention. The interaction term will be the main parameter of interest for assessing intervention effectiveness. To account for the multilevel design, the model will include a random intercept for each participant to account for repeated measures, a random intercept for each school to adjust for within-school clustering, and a fixed effect for country to control for systematic differences across national contexts. Other covariates associated with the outcome may be included in the model as fixed effects, depending on the objective. All models will be adjusted for the sex and age of the student.

The effectiveness analyses will be carried out following the intention-to-treat principle. In addition, a complete case analysis will be conducted as a sensitivity analysis to assess the robustness of the findings. Differences between included and excluded participants will be examined to explore potential bias due to missing data.

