### Mediation analysis

Mediation analysis will be performed using structural equation modelling to assess whether the effect of the intervention on the primary outcome is mediated by one or more intermediate variables (mediators) such as the secondary outcomes or other variables.

All available data will be included under the assumption that data are missing at random. All statistical tests will be two-sided, and a p value ≤0.05 will be considered indicative of statistical significance. Effect estimates will be reported with corresponding 95% CIs to indicate the precision of the estimates. The analysis will be conducted with SAS (V.9.4) and/or R software.

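### The baseline comparison of arms uses χ² and t-tests that ignore the randomised schools, so its p values are not valid as written

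*Protocol article*

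**What the plan says.** The Statistical analyses section first lists descriptive summaries and then fixes the between-arm comparison: "To evaluate baseline differences between the intervention and control groups the χ^2^ test or t-test will be applied". No allowance for school is mentioned. The general rule on testing, placed at the end of the Mediation analysis section, is: "All statistical tests will be two-sided, and a p value ≤0.05 will be considered indicative of statistical significance".

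The section on blinding, randomisation and allocation concealment makes the school the randomised unit. An external statistician "conducted the randomisation of schools into the intervention and control groups using a computer-based random number generator", and "the statistician conducted a block randomisation at the country level in groups of four to eight schools". The same section gives the order of events: "The randomisation occurred before baseline assessments since we needed to be able to tailor the explanation and information of the project to participants". It adds: "After the randomisation, the research team and participants were not blinded regarding school allocation". The section on implementation strategies says of the introductions made to pupils, families and teachers during recruitment: "In intervention schools, available intervention resources were highlighted".

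Clustering is recognised in two other places. The Sample size section assumes an ICC of 0.20 for schools and countries combined, 200 pupils per school, and 50% lost to refusal or follow-up. The Effectiveness analysis section puts a school random intercept and a country fixed effect in the outcome model.

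**The concern.** Pupils in one school resemble each other more than pupils in different schools, and whole schools went to one arm or the other. A pupil-level χ² or t-test takes its standard error from the number of pupils, when the randomised number is about 50 schools. The standard error is too small, and the test will often call ordinary school-to-school variation a difference between arms.

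In many trials this would only spoil a column of p values in the baseline table. Here baseline comparability carries more weight. Allocation was known before pupils were enrolled, the information they received differed by arm, and the sample size calculation allows for heavy refusal. Who joined could therefore differ by arm. A reader who turns to the baseline p values for reassurance cannot tell whether a small one reflects selective recruitment or the variation expected when schools are randomised.

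**Working it through.** The article states no error rate for these tests, so there is no figure of the plan's own to reproduce.

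**Inputs**
- Two-sided 5% level, critical value 1.96 (rule on testing).
- ICC 0.20, schools and countries combined, for mental health scores (Sample size).
- Participating pupils per school, m = 200 × 50% = 100 (Sample size).
- Schools blocked within four countries. The country counts are 7, 15, 15 and 13, which sum to 50, while the stated total is 51 (School recruitment and selection). The difference does not matter here.

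**Step 1. Whole ICC between schools.** The variance of the difference between arms is inflated by D = 1 + (m − 1) × ICC. The chance of a false rejection is 2 × [1 − Φ(1.96/√D)].

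D = 1 + 99 × 0.20 = 20.8, √D = 4.56, 1.96/4.56 = 0.430, rate = 66.7%.

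Other cluster sizes at ICC 0.20:

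| Pupils per school | D | False rejection |
|---|---|---|
| 94 (6000/64) | 19.6 | 65.8% |
| 100 | 20.8 | 66.7% |
| 118 (6000/51) | 24.4 | 69.2% |
| 200 | 40.8 | 75.9% |

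**Step 2. Allow for the country part.** Blocking by country nearly balances countries between arms, so the country share adds little to the difference. It still enters the pooled variance that the t-test uses. With total variance 1, the inflation becomes about D = m × (school share) + (within-school share), the last being 0.80. Null trials were also simulated with schools blocked within the four country counts, 3000 per setting.

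| School / country share | D (m = 100) | Formula | Simulation |
|---|---|---|---|
| 0.20 / 0 | 20.8 | 66.7% | 66.9% |
| 0.15 / 0.05 | 15.8 | 62.2% | 63% |
| 0.10 / 0.10 | 10.8 | 55.1% | 56% |
| 0.05 / 0.15 | 5.8 | 41.6% | 44% |

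The simulated rates tend to be slightly higher, as expected with odd numbers of schools per country, which cannot be split equally.

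**Step 3. Other baseline variables.** The article gives no ICC for sex, age, family affluence or the rest. Assumed school ICCs with m = 100 and no country part, by the Step 1 formula:

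| Assumed ICC | D | False rejection |
|---|---|---|
| 0.01 | 1.99 | 16.5% |
| 0.02 | 2.98 | 25.6% |
| 0.05 | 5.95 | 42.2% |

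**Step 4. Does a cluster-aware test repair this?** In the same simulations, a school-level comparison with country as a fixed effect rejected in 4.5% to 5.9% of null trials across all settings.

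**Step 5. What that test can detect.** With 51 schools, SE = √[4 × (school share + within-school share/m)/51], and 80% power needs a true imbalance of about 2.8 × SE.
- School share 0.20: √[4 × (0.20 + 0.80/100)/51] = 0.128, so about 0.36 SD.
- School share 0.10, country share 0.10: √[4 × (0.10 + 0.80/100)/51] = 0.092, so about 0.26 SD.

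**The case against.** The strongest reply is that the consequences are small. The comparison sits among descriptive analyses, and the article never calls it a check on recruitment bias. The outcome model has a school random intercept and a country effect and targets the group-by-time interaction. This stands: the primary estimate is not directly affected, and the link to recruitment bias is an inference from the design.

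A second reply is that 67% overstates the rate for this design, because 0.20 includes country and country was blocked. This also stands, and 44% to 63% is the better range for mental health scores. Even so, the lowest rate computed, 16.5% at an assumed ICC of 0.01, is more than three times the nominal 5%.

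Three stronger readings are tempting, and the article does not support them.
- A reader might infer that covariates will be picked on these p values. The Effectiveness analysis section says: "Other covariates associated with the outcome may be included in the model as fixed effects, depending on the objective". That criterion is association with the outcome, and nothing connects it to the baseline tests.
- A reader might infer that most baseline variables will look imbalanced. That needs a school ICC near 0.10 or above for each variable, which the article does not give.
- A reader might infer that participation by arm will go unexamined. The article commits to CONSORT reporting, and this is detail that an article commonly leaves to the full protocol or analysis plan.

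**Conclusion.** The point holds for the named tests. As written, the baseline p values are not valid, because they count pupils as independent in a trial that randomised schools. With 100 participating pupils per school, the chance of a false rejection for mental health scores is about 67% if the whole ICC of 0.20 is between schools. It is about 44% to 63% once a country share of 0.05 to 0.15 is taken out. For variables with an assumed school ICC of 0.01 to 0.05 it is about 16% to 42%.

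These figures rest on the article's ICC and on equal cluster sizes. The country split and the lower ICCs are assumptions. The 67% is not a strict ceiling, since larger clusters at the same ICC give more.

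The harm lies in interpretation. Where pupils joined after unblinded allocation, the tests cannot distinguish selective recruitment from ordinary differences between schools. This should be corrected, but it does not threaten the primary effect estimate.

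**What to change.** Replace the sentence on χ² and t-tests. Present baseline characteristics by arm descriptively, with standardised differences. Where a test is wanted, use a mixed model with a school random intercept (or its counterpart for categorical variables) or a comparison of school-level summaries, in either case adjusted for country.

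The cost is analysis wording only, with no new data. The downside is limited power: by Step 5, about 50 schools give 80% power only for imbalances of roughly 0.26 to 0.36 SD in mental health scores at school shares of 0.10 to 0.20. A non-significant result should therefore not be read as evidence that recruitment was unselective.
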